### Assessments

Patients will be assessed prior to randomization (baseline) and at follow-up visits at 3, 6, 9, 12, 18, 24, 30 and 36 months post randomization. Assessments will require that patients visit the local investigational center and have their data collected via an electronic case report form. Table 3 provides a summary of the data collection process and timing.

**Table 3 T3:** SubQStim study: summary of data collection

**Study requirements**	**Screening**	**Baseline**	**Test stimulation implant**	**Permanent implant**	**Wound check**	**1 month**	**3 months**	**6 months**	**9 months**	**12 months**	**18 and 24 months**	**30 and 36 months**	**Unscheduled**	**Discontinued**
Patient informed consent/patient information sheet	X													
Screening inclusion/exclusion criteria	X													
Demographics	X													
Physical examination	X													
Medical history	X													
HCU history	X													
VAS (point in time measurement only)	X												X	X
Back pain map	X		X^a^	X^a^	X	X	X	X	X	X	X	X	X	X
Paresthesia map (implanted subjects only)			X	X^a^	X	X	X	X	X	X	X	X	X	X
Confirmation of 7-day baseline dairy inclusion criteria		X												
Randomization assignment (after questionnaires)		X												
HADS		X												
painDETECT		X												
EQ-5D		X					X	X	X	X	X	X	X	X
ODI		X					X	X	X	X	X	X		
SF-36		X					X	X	X	X	X	X		
PGIC		X					X	X	X	X	X	X	X	X
Implant information			X^a^	X^a^										
Postoperative radiography				X										
Subject satisfaction							X	X	X	X	X	X	X	X
7-day diary completion							X	X	X	X	X	X		
Initial and final interrogations and uploads			X	X	X	X	X	X	X	X	X	X	X	X
Medication assessment		X	X	X	X	X	X	X	X	X	X	X	X	X
Protocol deviations		X	X	X	X	X	X	X	X	X	X	X	X	X
Event assessment (adverse events)		X	X	X	X	X	X	X	X	X	X	X	X	X
HCU		X	X	X	X	X	X	X	X	X	X	X	X	X

*EQ-5D* EuroQoL five dimensions, *HADS* Hospital Anxiety and Depression Scale, *HCU* healthcare utilization, *ODI* Oswestry Disability Index, *PGIC* Patient Global Impression of Change, *SF-36* Short-Form 36, *VAS* visual analog scale. ^a^Pre-implant and post-implant as indicated; otherwise, post-implant or post-reprogramming only.

#### *Primary outcome*

The proportion of subjects with a ≥50% reduction in back pain intensity (VAS) from baseline to the 9 months post randomization. Patients will complete a pain diary, comprising a VAS scale, three times daily during the 7 days prior to their visit. The average VAS during that period will be calculated as the ratio between the sum of recorded VAS and the number of VAS measured. The percentage pain reduction will be calculated as 100*(VAS_0_-VAS_V_)/VAS_0_, where VAS_0_ is the average VAS at baseline visit and VAS_v_ is the average VAS at subsequent visits.

#### *Secondary outcomes*

Secondary outcomes are: pain relief: ≥50% back pain relief at all visits in addition to 9 months, ≥30% back pain relief at all time points; pain intensity score: back and leg VAS score via patient diary at all time points; functional disability: Oswestry Disability Index (ODI) version 2 [24] at all time points; health-related quality of life: Short-Form 36 (SF-36) [25] and EQ-5D-5 L [26] at all time points; patient satisfaction (‘are you satisfied with the pain relief provided by your treatment?’ and ‘based on your experience so far, would you have agreed to this treatment?’) [7] at all follow-up time points; Patient Global Impression of Change (PGIC) [27] at all follow-up time points; healthcare utilization (HCU), that is, concomitant drug treatment for pain relief (opioid, non-steroidal anti-inflammatory drugs (NSAIDs), antidepressant drugs, anticonvulsants), need for physical therapy or other non-drug treatments) [28] at all time points; adverse events: both device-related and non-device-related adverse events and complications will be collected. The nature and frequency of events will be documented and an Adverse Events Committee will adjudicate all events.

#### *Process measures*

At the screening and baseline visits, the following additional information will be collected: patient demographics (for example, age, gender, duration of back pain), neuropathic pain severity (Douleur Neuropathique en 4 Questions (DN4)), [29] mood (Hospital Anxiety and Depression Scale (HADS)) [30] and level of previous healthcare utilization. Patients who proceed to device implantation will have the following information collected: back pain and paresthesia maps, radiographic images, parameter settings, lead location, and device implant information (that is, model, serial number). At subsequent visits, clinical and patient programmer data will be downloaded. All medical and alternative treatments received as optimized medical management will be recorded at each follow-up visit.

Unscheduled patient visits could occur between scheduled study follow-up visits for the following reasons: patient discontinuation from the study, device reprogramming and management of device-related complications, or revisions of non-device treatment.

### Sample size and power calculations

A 20% difference in the primary outcome between the SQS and OMM arms is considered relevant. Assuming that 40% of the patients receiving OMM alone achieve the primary outcome, the study needs to recruit a total of 350 patients to detect a clinically important difference at the 5% alpha level and 90% power allowing for 20% attrition. However, it is expected that the difference between the two arms of the trial may be larger, that is, 25% or 30%. Two interim analyses are, therefore, planned at 140 and 220 evaluable patients (that is, with completed primary outcome) to provide 80% power in order to detect a 30% difference, and 85% power to detect a 25% difference (respectively), at 2-sided 1% alpha level. In order to ensure an overall alpha of two-sided 5%, the final analysis will be performed at two-sided 3% alpha [31]. In order to undertake 2 interim analyses and a final analysis, a total of 400 patients (N = 200 SQS arm and N = 200 OMM arm) will be required. These interim and final analyses are summarized in Table 4.

**Table 4 T4:** SubQStim study: sample size and power calculations

**Analysis**	**Expected difference between groups**	**Power (1-β)**	**Nominal error risk (α)**	**Proportion of responders**		**Sample size**	
				**OMM arm**	**SQS arm**	**Evaluable patients**^**a**^	**Enrolled (20% attrition rate)**
Interim 1	30%	80%	1%	35%	65%	140	176
Interim 2	25%	85%	1%	37.5%	62.5%	220	276
Final	20%	90%	3%	40%	60%	314	392
For reference: one-shot analysis	20%	90%	5%	40%	60%	280	350

^a^Patients with completed primary outcome data.

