## Trial status

The SubQStim trial began patient recruitment in November 2012. Recruitment is expected to close in late 2014. It is anticipated that primary endpoint findings will be available in approximately 2016.

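### The additive 1% + 1% + 3% split is valid but conservative: overall alpha is about 3.9%, so the 3% final level is stricter than a 5% guarantee needs

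*Protocol article*

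**What the plan says.** The section on sample size and power calculations in the protocol article sets the whole group-sequential scheme. On the number and timing of looks: "Two interim analyses are, therefore, planned at 140 and 220 evaluable patients". On the interim level, which applies to both looks: "85% power to detect a 25% difference (respectively), at 2-sided 1% alpha level". On the final level: "In order to ensure an overall alpha of two-sided 5%, the final analysis will be performed at two-sided 3% alpha", with a literature reference that is not available here.

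Table 4 carries the same levels into the sample size: 140 evaluable at the first interim, 220 at the second, 314 at the final analysis (392 enrolled). It also gives a reference row without interim looks: 280 evaluable, 350 enrolled, at 5%. The total is then rounded up: "In order to undertake 2 interim analyses and a final analysis, a total of 400 patients". No allowance for correlation between the looks is described.

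**The concern.** The three levels add to exactly 5%. Simple addition is the exact overall error only if the three rejection events never overlap. Here they overlap heavily: the first 140 patients are contained in the 220, and the 220 in the 314. A chance excess at one look tends to persist to the next, so the probability of rejecting at least once falls well short of the sum.

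At stake is unused alpha. The final analysis is held to a stricter level than the stated guarantee requires, and Table 4 pays for this in patients, half of whom are randomized to an arm with an implant procedure. The same 5% guarantee could be met with fewer patients, or with more power at the same size.

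**Working it through.** **Inputs** (Table 4 and surrounding text): looks at 140, 220 and 314 evaluable patients; two-sided levels 1%, 1%, 3%; 1:1 allocation; responders 40% vs 60% at the final analysis, power 90%; attrition 20%.

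**Step 1: reproduce Table 4.** Per-arm size without continuity correction is n0 = [z(1−α/2)·√(2p̄(1−p̄)) + z(1−β)·√(p1q1 + p2q2)]² / d². With correction it is n = (n0/4)·[1 + √(1 + 4/(n0·d))]².

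Final row: z = 2.170 and 1.282, p̄ = 0.5, d = 0.2. So n0 = (2.170 × 0.7071 + 1.282 × 0.6928)² / 0.04 = 146.7, and n = 156.5, rounded up to 157 per arm, or 314.

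| Row | Stated evaluable | Corrected formula, unrounded | Rounded up per arm |
|---|---|---|---|
| Interim 1 | 140 | 139.9 | 140 |
| Interim 2 | 220 | 220.7 | 222 |
| Final | 314 | 313.1 | 314 |
| One-shot | 280 | 278.1 | 280 |

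Without the correction the totals would be 128, 206, 294 and 260, so Table 4 implies a continuity-corrected test.

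**Step 2: reproduce the 5%.** 1% + 1% + 3% = 5%. If the looks were independent: 1 − 0.99 × 0.99 × 0.97 = 4.93%.

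**Step 3: actual overall alpha.** For cumulative looks, corr(Zi, Zj) = √(ni/nj): √(140/220) = 0.798, √(140/314) = 0.668, √(220/314) = 0.837. Numerical integration of the joint normal distribution, counting a crossing at any look as a rejection, gives first-crossing probabilities of 1.00%, 0.67% and 2.20%. The total is 3.87%.

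**Step 4: the final level that exhausts 5%, with both interims at 1%.**

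| Final look (evaluable) | Overall alpha at 1/1/3 | Final level for 5% overall |
|---|---|---|
| 314 | 3.87% | 4.26% |
| 320 (400 less 20%) | 3.89% | 4.24% |
| 400 (no attrition) | 4.07% | 4.02% |

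**Step 5: the gain, in Table 4's own formula.** At 157 per arm, corrected power = Φ{[(d − 1/n)·√n − z(1−α/2)·√(2p̄(1−p̄))] / √(p1q1 + p2q2)}.
- At 3%: Φ[(2.426 − 1.534)/0.693] = Φ(1.287) = 90.1%.
- At 4.26% (z = 2.027): Φ[(2.426 − 1.434)/0.693] = Φ(1.433) = 92.4%; at 4.2% it is 92.3%.

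Without the correction the rise is from 92.0% to 93.9%.

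For 90% power at 4.26%: n0 = 134.7, n = 144.6, so 145 per arm. That is 290 evaluable and 290/0.8 = 362.5, or 363 enrolled. The saving is 314 − 290 = 24 evaluable, or 392 − 363 = 29 enrolled.

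**Step 6: is a fixed 4.2% safe?** Not in general. With levels 1/1/4.2, overall alpha is 4.9% at 140/220/314, but about 5.2% at 140/220/400 and about 5.2% at 100/200/340. Discreteness also matters. Simulating the uncorrected two-proportion z-test at 140/220/314 with both arms at 40% gives about 5.1%. The continuity-corrected test in the same setting (2 million trials) gives about 3.8%.

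**The case against.** The strongest reply is that nothing in the protocol is false. An additive split does ensure at most 5%, whatever the correlation, look timing or attrition. This stands. A reader might infer from the 3.9% that the 5% statement is an arithmetic error or that error control has failed. The document does not support that: it promises a guarantee, and the guarantee holds.

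Second, the trial is already sized for the 3% level. Table 4 reaches 90% power at 314 evaluable patients, shows the one-shot design alongside, and the total is rounded up to 400. No claimed power is missing. This also stands; the gain is about 2 points above a target already met, or about 29 fewer enrolled.

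Third, the simple split is robust: it needs no recomputation when looks move, whereas a fixed 4.2% can exceed 5% (Step 6). This stands against writing 4.2% into the plan, but not against a rule evaluated at the actual looks. The unseen analysis plan might refine the final boundary, but the protocol itself states the 3% and sizes the trial on it.

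A reader might also infer that the second interim should be dropped because its 220 evaluable patients would arrive after enrollment has ended ("Recruitment is expected to close in late 2014"), or that the sequential design expects to enroll more than the one-shot 350. Neither is supported. Both need an accrual curve the article does not give, and uniform accrual is only an assumption. The enrollment comparison was unfavorable only for a 20-point difference, while the interims were added because 25 or 30 points was thought possible. Dropping the second look would also lose an early read-out, so that is a trade-off, not a defect.

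**Conclusion.** The point holds as one of efficiency. As written, type I error is controlled and the design is valid. The overall two-sided alpha at the planned looks is about 3.9%, about 1.1 percentage points below the stated 5%, and the 3% final level is stricter than that guarantee requires. The cost is about 2 points of power at 314 evaluable patients, or about 24 evaluable (29 enrolled) patients at 90% power. Of the 34 evaluable patients that Table 4 adds to the one-shot design (314 − 280), about 24 therefore come from the additive split and about 10 from the interim looks themselves.

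These figures assume the normal approximation, looks at 140, 220 and 314 evaluable patients, rejection possible at every look, and the 40% vs 60% planning rates. The exact final level depends on where the looks fall: about 4.2% to 4.3% at 314 and about 4.0% at 400.

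**What to change.** Keep two-sided 1% at each interim. Before the first look, replace the fixed 3% by a rule: the final level is computed by an alpha-spending function, or from the joint distribution of the three statistics, at the information fractions actually observed, so that overall two-sided alpha is 5%. Give about 4.2% (140/220/314) and about 4.0% (140/220/400) as illustrations only. Name a final test that holds its level, such as the continuity-corrected one implied by Table 4.

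Update the final row of Table 4 to show either about 92% power at 314 evaluable patients, or 90% power at about 290 evaluable (363 enrolled). The sponsor can choose between the two.

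The cost is one recalculation and a table edit before the first look, with no added patients. The small downside is that the final level must be recomputed if the looks shift, which the additive split does not require. If the sponsor prefers that simplicity, it would be enough to say that 5% is an upper bound and that the overall alpha at the planned looks is about 3.9%.

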### Procedures to minimize bias

Computer generated random allocation schedules will be preprepared for each investigational center. The randomization schedule will be centrally held and allocation concealment will be maintained by an online database system that automatically assigns the patient to one of the two arms on confirmation by research nurse at the end of the baseline visit. The randomization schedules will be stratified to maintain a 1:1 balance between the treatment and control arm within each center and in the study as a whole. Patients will be randomized sequentially based upon randomization date and time.

Given the nature of both the intervention and control treatments, it is unfortunately not possible to blind either patients, or clinicians.

If a patient misses a study visit, the center’s study staff will make three attempts (one in writing and sent via a traceable method) to bring them in for a study visit. The numbers and reasons for dropouts and losses to follow-up will be reported by each arm of the study.

All study deviations (that is, an event where the investigator, or center personnel, did not conduct the study according to the Clinical Investigational Plan, Protocol, or Clinical Investigation Agreement) will be recorded and the reasons documented.

### Data analysis

#### *Statistical analysis*

The intent-to-treat patient set (ITT) consists of all patients as they were randomized into the study. The per-treatment patient set (PT) consists of all patients of the ITT patient set for whom no major protocol deviation was reported. Patients who underwent a treatment switch, that is, who had initially been randomized to the OMM arm and switched to the SQS arm, or *vice versa*, will be included in this patient set. They will be analyzed according to treatment actually received.

The primary effectiveness analysis will be based on a between group comparison of primary and secondary outcomes up to, and including, the 9-month visit using the ITT patient data set [32]. For continuous outcomes, analytic models will be adjusted for baseline outcome score.

Sensitivity analyses will be undertaken using the same analytic models used in the primary analysis and based on the PT data set. In case of a discrepancy between the two analyses, a closer analysis of the data, of those patients from which the discrepancies result, will be performed. An additional sensitivity ‘modified ITT’ analysis will be performed for the primary outcome, considering patients randomized to the SQS arm but not definitively implanted as ‘failures’.

In phase II of the study (beyond 9-month visit) the analytic focus will be a within-person approach, that is, comparison of primary and secondary outcomes at follow-up, relative to baseline. In addition, the percentage of subjects who switched treatments after the 9-month follow-up visit, and the time to switchover, will be compared between OMM and SQS arms.

The study will seek to minimize missing data by conducting completeness checks on study data and patient questionnaires, with follow-up on any missing data. It is not possible to predict which will be the most effective method, therefore, we will undertake sensitivity analyses to examine different methods of missing data imputation, such as mean of nearby points (moving average), last value carried forward, doubly robust estimators or the best or the worst values that are not in favor of the SQS arm [33,34].

The ‘safety patient set’ consists of all patients of the ITT dataset, who started any of the study procedures independent of the treatment they had been randomized to. Complications and adverse events will be reported descriptively.

All statistical tests will be interpreted at the two-sided α = 5% level and results reported as means and 95% confidence intervals. A more detailed exposition of study statistical analyses will be presented in a Statistical Analysis Plan to be completed prior to any data analysis.

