### Aims and objectives

The SubQStim study is a multicenter RCT comparing the clinical effectiveness of peripheral nerve stimulation utilizing a subcutaneous lead implant technique plus optimized medical management (‘SQS arm’) versus optimal medical management alone (‘OMM arm’). Patients with back pain due to FBSS will be randomized to the SQS or OMM arms. Patients that fail to achieve the primary outcome (that is, ≥50% reduction in back pain intensity) at 9 months post randomization will be allowed to switch treatments. All patients will be followed up for 36 months post randomization.

The primary objective of SubQStim study is to compare the proportion of patients achieving the primary outcome at 9 months post randomization in SQS and OMM arms. Secondary objectives are to: (1) compare the primary outcome between SQS and OMM arms at 3 months and 6 months post randomization; (2) compare secondary outcomes (functional disability, health-related quality of life, patient satisfaction, patient global impression of change, healthcare utilization/costs, use of pain mediation and non-invasive pain treatment) between SQS and OMM arms at 3, 6 and 9 months post randomization; (3) assess the value of trial stimulation in predicting 9-month post-randomization primary outcome response in the SQS arm; (4) assess the trend in device programming parameters up to 9 months post randomization; (5) assess within-patient changes (that is, compared to baseline/prior to randomization) in primary and secondary outcomes from 9 to 36 months post randomization; (6) quantify the level of SQS-related and non-SQS related adverse events at all follow-up timings up to 36 months post randomization.

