## Methods/Design

### Design and setting

Patients will be randomized 1:1 to peripheral nerve stimulation utilizing a subcutaneous lead implant technique plus optimized medical management (‘SQS arm’) or optimized medical management alone (‘OMM arm’) and followed for 9 months (period I: randomized comparative period). At 9 months after randomization, if patients in either arm fail to meet certain criteria (see below) they may switch treatment; that is, those in the OMM arm receive SQS or those in the SQS arm have their device turned off and/or explanted. Patients will be followed up until 36 months post randomization (period II: long-term follow-up period). The study design is summarized in Figure 1.

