### Treatment switch criteria

The investigator criteria to inform patient treatment switch after 9 months post randomization or later are as follows: if <30% pain relief on VAS: switchover is normally allowed without any further justification; if 30% to 50% pain relief on VAS: switchover is normally allowed if the patient has another reason for not responding to randomized arm, such as: no perceived improvement in quality of life, disability or medication use and/or side effects from treatments; if >50% pain relief on VAS: switchover is normally not allowed.

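### The fixed pre-randomization reference in phase II keeps relief already present on OMM inside switchers' post-switch change, so that change cannot by itself show what SQS added

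*Protocol article*

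**What the plan says.** Three places in the protocol article fix the long-term reference.

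- **Statistical analysis:** phase II is a within-person "comparison of primary and secondary outcomes at follow-up, relative to baseline".
- **Aims and objectives, objective 5:** the aim is to "assess within-patient changes (that is, compared to baseline/prior to randomization) in primary and secondary outcomes from 9 to 36 months post randomization".
- **Primary outcome:** in the percentage-reduction formula, VAS₀ "is the average VAS at baseline visit and VAS_v_ is the average VAS at subsequent visits".

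Under Design and setting, a treatment switch means that "those in the OMM arm receive SQS or those in the SQS arm have their device turned off and/or explanted". Treatment switch criteria sets two bands in which a switch is possible: "if <30% pain relief on VAS: switchover is normally allowed without any further justification", and "if 30% to 50% pain relief on VAS: switchover is normally allowed if the patient has another reason for not responding to randomized arm". Above 50% relief a switch is normally ruled out. Secondary outcomes carries the ≥50% and ≥30% relief thresholds to the other visits. Table 3 schedules the 7-day diary at 9 months and at the later visits.

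No section gives switchers a second reference or a comparison of after the switch with before it.

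**The concern.** A patient who moves from OMM to SQS has one VAS₀, measured before either treatment began. The change from that value at, say, 24 months adds two things together: what had already happened on OMM by the time of the switch, and what happened after SQS was added. The stated analysis does not separate them.

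After month 9 the main analysis is within-patient, so no randomized contrast separates them either. If the figures for this group are read as the result of SQS, a device that added nothing would still show mean relief and some responders. The longer-term economic analyses cover the same period.

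**Working it through.** **Inputs from the protocol.** Relief at a visit is 100 × (VAS₀ − VASᵥ)/VAS₀, with VAS₀ fixed at baseline. Switching is possible at r < 30%, and conditionally at 30–50%, where r is relief at 9 months. The final-analysis row of Table 4 assumes that 40% of OMM patients reach ≥50% relief. The documents give no switch rate, no distribution of 9-month relief and no visit-to-visit variance.

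**Step 1: further fall needed to become a ≥50% responder.** The pre-switch score is (1 − r)VAS₀ and the responder threshold is 0.5 VAS₀. The further fall needed, as a share of the pre-switch score, is (0.5 − r)/(1 − r).

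| Relief on OMM at switch, r | Calculation | Further fall needed |
|---|---|---|
| 10% | 0.40/0.90 | 44.4% |
| 20% | 0.30/0.80 | 37.5% |
| 30% | 0.20/0.70 | 28.6% |
| 40% | 0.10/0.60 | 16.7% |
| 45% | 0.05/0.55 | 9.1% |

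With the pre-switch score as reference, the fall needed is always 50%. For example, take an assumed VAS₀ of 70 mm and r = 40%. The pre-switch score is 0.60 × 70 = 42 mm and the threshold is 35 mm. A further 7 mm makes a responder under the stated rule, against 21 mm with the pre-switch reference.

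**Step 2: the ≥30% outcome.** A switcher with 30–50% relief already meets it before implant, whatever SQS then does.

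Steps 1 and 2 are arithmetic on the protocol's own formula and switch bands.

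**Step 3: size if SQS adds nothing.** This step needs assumptions. I simulated 2 million OMM patients per scenario. True relief was stable, with mean 42% and SD 25 or 30 points, and visit noise was independent with SD 10 or 15 points. The switch was decided on observed 9-month relief, and the later visit was drawn with no SQS effect. Points are percentage points of baseline VAS. Observed 9-month response came out at 38–41%, in line with the protocol's 40%.

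| Who switches | Mean relief against baseline | ≥50% responders against baseline | Mean change against month 9 | ≥50% responders against month 9 |
|---|---|---|---|---|
| All below 30% | 12–19 points | 2–8% | 3–8 points | 0.2–3.5% |
| All below 50% (upper bound) | 24–28 points | 12–19% | 2–5 points | 1–5% |

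For the ≥30% outcome, across both rows, 19–49% are responders against baseline and 4–18% against month 9.

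**Step 4: comparing the two references.** The change against month 9 in this simulation is regression to the mean: patients are selected for a poor 9-month score and drift back. The change against baseline contains that drift plus the relief already present. The ratio of the two means depends on the scenario. In the <30% band it is about 2 with noise SD 15 (14–19 points against 7–8) and about 4 with noise SD 10. It reaches about 12 only when everyone below 50% switches and noise SD is 10.

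**The case against.** The strongest reply is that a common baseline has a proper purpose. SQS is always given on top of OMM, so patients randomized to SQS also have OMM benefit inside their change from baseline. One VAS₀ puts all groups on the same scale and describes each patient's total course. A pre-switch reference asks a different question, what was added after the switch, so choosing it is partly a choice of estimand. It brings its own regression to the mean, and neither reference is a randomized comparison. All of this stands. It is a reason to report both references rather than replace one.

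A reader might infer that the protocol credits relief gained on OMM to the device. It does not say so. Objective 5 speaks of within-patient change for all patients, including those whose device is switched off or removed. The sentence "They will be analyzed according to treatment actually received" belongs to the definition of the per-treatment set. The stated use of that set is a sensitivity analysis with the primary models, and no section assigns it to phase II.

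A reader might also take the 60% of OMM patients expected to miss the primary outcome (100% − 40%) as the expected number of switchers. It is only a ceiling on candidates. The 30–50% band needs a further reason, and in the simulation about a third of patients fall below 30%.

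Finally, extra tables are ordinary SAP content, and the unseen SAP may contain this one. That is fair for the table. The choice of reference, however, is stated in the protocol rather than left open.

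**Conclusion.** The point holds in a limited form. The protocol fixes the pre-randomization baseline for everyone in phase II and allows OMM patients with up to about 50% relief to switch. For OMM-to-SQS switchers, change from baseline therefore includes any relief already present on OMM and cannot by itself show what SQS added.

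How large this is depends on who switches. The <30% row of the simulation is the more cautious guide, because no further justification is needed there. The <50% row is an upper bound, because it has every patient in the conditional band switching. Both rows rest on assumed variances, stable true relief and no SQS effect. Carried-over relief may be small, nil or negative for individual patients in the <30% band. It would go too far to call the pre-switch bias negligible beside the other, since the ratio is only about 2 in some scenarios.

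The 9-month primary comparison and the 9-month primary economic analysis are unaffected. Change from baseline remains valid as a description of total course. This is a cheap improvement to secondary, uncontrolled follow-up, not a flaw in the main result.

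**What to change.** In the phase II paragraph, or in the SAP:

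1. Keep change from the pre-randomization baseline for all patients, labelled as a description of total course.
2. Report phase II results by randomized arm and switch status.
3. For OMM-to-SQS switchers, add change from the last 7-day diary before the switch beside change from baseline. This is normally the 9-month diary, which is already collected.
4. State that switchers' change from baseline is not to be interpreted as an SQS effect, that regression to the mean affects both references, and that neither is a randomized comparison.

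The cost is some wording and one extra table, with no new data. The long-term figures for switchers will look less favourable.

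### The analysis section's blanket two-sided 5% level and 95% intervals contradict the 1%, 1% and 3% levels set for the primary outcome

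*Protocol article*

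**What the plan says.** The section on sample size and power sets up a three-look design. "Two interim analyses are, therefore, planned at 140 and 220 evaluable patients", and the interim tests are described as giving 80% power for a 30-point difference and "85% power to detect a 25% difference (respectively), at 2-sided 1% alpha level". It then fixes the last look: "In order to ensure an overall alpha of two-sided 5%, the final analysis will be performed at two-sided 3% alpha". Table 4 repeats the levels row by row: 1%, 1% and 3% at 140, 220 and 314 evaluable patients. A 5% level appears in that table only in the reference row for a single analysis without interim looks (280 evaluable).

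The Statistical analysis section defines the primary effectiveness analysis as the between-arm comparison of primary and secondary outcomes up to 9 months in the ITT set. It closes with "All statistical tests will be interpreted at the two-sided α = 5% level and results reported as means and 95% confidence intervals". That sentence does not exempt the primary outcome or the interim looks, and does not refer back to the sample size section. The next sentence leaves further detail to a statistical analysis plan that is to be finished before any data analysis.

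**The concern.** The two sections give different decision rules for the same test. The primary outcome falls within the scope of the closing sentence, because the section it closes covers the primary comparison. Read literally, that sentence applies to a three-look trial the level that Table 4 reserves for a design with one look.

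Two things are at stake. The first is the threshold for declaring success on the primary outcome, at the interims and at the end. The second is whether the reported interval agrees with the test: an ordinary 95% interval corresponds to a 5% test, so it can exclude zero when the prescribed 1% or 3% test is not significant. In an open-label trial with interim looks, it should not be possible to choose the threshold after seeing data.

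**Working it through.** **Inputs.** Looks at 140, 220 and 314 evaluable patients (Table 4), 1:1 allocation, hence 70, 110 and 157 per arm. Levels of 1%, 1% and 3% (sample size section) against 5% (Statistical analysis section). Two-sided critical values are 2.576 (1%), 2.170 (3%) and 1.960 (5%).

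**Step 1: the plan's own figures.** The levels add up: 0.01 + 0.01 + 0.03 = 0.05. For Table 4, the usual pooled-variance two-proportion formula gives n per arm as

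n = [z(1−α/2)·√(2p̄(1−p̄)) + z(1−β)·√(p1(1−p1) + p2(1−p2))]² / d²,

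and the continuity-corrected size is n' = (n/4)·[1 + √(1 + 4/(n·d))]².

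| Row | Uncorrected total | Corrected total | Table 4 |
|---|---|---|---|
| Interim 1 (35% v 65%, α 1%, power 80%) | 128 | 140 | 140 |
| Interim 2 (37.5% v 62.5%, 1%, 85%) | 206 | 222 | 220 |
| Final (40% v 60%, 3%, 90%) | 294 | 314 | 314 |
| One-shot (40% v 60%, 5%, 90%) | 260 | 280 | 280 |

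Table 4 therefore follows a continuity-corrected calculation, and the final size rests on the 3% level.

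**Step 2: overall type I error, uncorrected normal test.** The three statistics are jointly normal with correlation √(n_i/n_j): √(140/220) = 0.798, √(140/314) = 0.668, √(220/314) = 0.837. Overall error is 1 − P(|Z1| < c1, |Z2| < c2, |Z3| < c3).

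- 1%/1%/3%: 3.9%
- 1%/1%/5%: 5.7%
- 5%/5%/5%: 10.1%

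A simulation of 4 million paths gives 3.88%, 5.69% and 10.09%. With both interims at 1%, the largest final level that keeps 5% overall is about 4.26%.

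**Step 3: the same with a continuity-corrected test.** Binomial trials simulated under the null at 70, 110 and 157 per arm, 2 million runs at each response rate of 30%, 40% and 50%:

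- 1%/1%/3%: 2.5% to 2.9%
- 1%/1%/5%: 4.0% to 4.2%
- 5%/5%/5%: 7.2% to 7.4%

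**Step 4: where the two rules disagree.** At a pooled rate of 50% the uncorrected boundary is z·√(2 × 0.25/n).

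- Final look: √(0.5/157) = 0.0564, so 2.170 × 0.0564 = 12.2 points at 3% and 1.960 × 0.0564 = 11.1 points at 5%.
- Interim 1: √(0.5/70) = 0.0845, so 21.8 points at 1% and 16.6 points at 5%.

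The continuity correction adds 1/n, at the final look 1/157 = 0.6 points, so that zone becomes about 11.7 to 12.9 points.

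**Step 5: intervals.** Suppose 88/157 against 70/157 respond at the final look, a difference of 18/157 = 11.5 points. With the standard error above, the 95% interval is 11.5 ± 11.1, or 0.4 to 22.5, and excludes zero. The 97% interval that matches the 3% test is 11.5 ± 12.2, or −0.8 to 23.7, and does not.

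**The case against.** The specific rule is clear and explained. The sample size section says why the final level is 3%, and Table 4 builds the sample size on it. The closing sentence of the analysis section looks like a general convention for all outcomes; its reference to means does not even suit a responder proportion. It may be meant for secondary outcomes, or as the overall 5% that the split protects. On the natural reading that the specific rule governs the primary outcome, alpha is preserved. This stands, and it limits the consequence. It does not remove the contradiction, because the sentence covers every test and attaches ordinary 95% intervals.

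A reader might infer that the trial's 5% overall alpha is broken, or that its true error rate is 10%. The documents do not support that. The 10.1% requires setting aside the explicit 1% for the interims. The 5.7% requires an uncorrected test, and the article does not name the analysis test. With the corrected test that fits Table 4, a 5% final look after 1% interims stays below 5%.

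The unseen analysis plan may settle the levels. But this is not detail left for later: the article states two incompatible rules, and an author of that plan could cite either.

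The practical effect is also modest. If the true rates are 40% and 60%, about 3% of trials reach the final look with a p-value between 3% and 5%.

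A reader might also ask for bias-adjusted estimates after early stopping. Overestimation on early stopping arises under the 1% interim level itself, so it is not a consequence of this contradiction.

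**Conclusion.** The point holds as an internal contradiction over the decision rule for the primary outcome. The levels in the sample size section are sound and conservative; the defect is the unrestricted wording of the analysis section. Its effect on type I error is conditional on which rule is followed, which looks are read at 5%, and which test is used. The 5% claim is clearly exceeded only if the interims are also read at 5% (about 10.1% uncorrected, about 7.2% corrected). If only the final look is affected, the rate is about 5.7% or about 4.1%. What does not depend on the test is that some final results, in a band roughly one percentage point wide, are positive under one section and negative under the other, and that a 95% interval can disagree with the prescribed test. The figures assume looks at exactly 140, 220 and 314 evaluable patients with equal arms; the boundaries also assume a pooled response rate of 50%.

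**What to change.** In the Statistical analysis section, limit the two-sided 5% level and 95% intervals to secondary and exploratory analyses. State that the primary outcome is tested only at the levels in the sample size section: two-sided 1% at each interim and 3% at the final analysis. Report it with matching intervals, 99% at the interims and 97% at the end, calculated by a method consistent with the test used. Settle this in the protocol and the analysis plan before any interim data are seen.

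The cost is a change of wording. Sample size, look times and alpha levels stay as they are. The downside is slightly wider intervals for the primary outcome: at the final look the multiplier rises from 1.960 to 2.170, about 11% wider (2.170/1.960 = 1.107).
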